### Exploratory outcomes

The exploratory outcomes will consist of the change between week 48 and 56 in the following: MDS-UPDRS part 3 ‘OFF’ scores, complete MDS-UPDRS (parts 1–4) ‘ON’ scores, total Levodopa equivalent daily dose, MoCA, MADRS, NMS-QUEST and PDQ-39.

The repeat assessments at week 56 (8 weeks after cessation of the study medication) will help to determine whether there is a sustained effect of UDCA on both motor and non-motor aspects of PD which would be in keeping with the assumption of a neuroprotective effect. Conversely, a rapid deterioration of these clinical parameters after cessation of the study drug would suggest a symptomatic effect of UDCA.

As an additional variable to be used in exploratory analysis a validated prognostic model calculating the risk of progression to an unfavourable outcome (either postural instability or dementia at 5 years) will be applied to each participant.^23^ We hope that this variable will account for some of the inherent heterogeneity among participants for their speed of clinical progression.

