### Secondary outcomes

The effect of UDCA versus placebo will be assessed as a change from baseline to week 48 for the following secondary outcomes:

Clinical assessment using the Movement Disorders Society Unified Parkinson’s Disease Rating Scale (MDS-UPDRS) Part 3 motor examination in the practically-defined ‘OFF’ medication state.In vivo measures of high and low energy metabolite levels (including adenosine triphosphate (ATP), phosphocreatine (PCr) and inorganic phosphate (Pi)) derived from multi-voxel brain ^31^P-MRS at baseline and week 48.Sensor-based, objective quantification of motor impairment using data collected with wearable sensors both in supervised (OptoGait and Opals systems, Sheffield patients only, Dynaport Movemonitor+, all patients) as well as in unsupervised real-life conditions (Dynaport Movemonitor+, all patients).

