### Motor measures

The MDS-UPDRS is currently the most used and validated clinical tool to quantify the disease state of an individual with PD.^18^ The minimal clinically important difference in the MDS-UPDRS part 3 is reported to be an improvement of 3.25 points for detecting minimal, but clinically pertinent, improvement and a deterioration of 4.63 points for observing minimal, but clinically pertinent, worsening.^24^ Over a period of 5 years, MDS-UPDRS part 3 scores were observed to increase (deteriorate) by 2.4 points per year.^25^ However, despite expected annual deterioration being well characterised, rate of decline may still depend on disease stage and therefore contemporaneous placebo control data remains essential to evaluate potential new therapies.

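### The exploratory outcomes are defined only as the week 48–56 change, which alone cannot show a sustained effect; six of the seven measures have no named treatment-period contrast

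*Protocol article*

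**What the plan says.** Protocol article, Exploratory outcomes: "The exploratory outcomes will consist of the change between week 48 and 56 in the following". The list has seven entries: MDS-UPDRS Part 3 OFF, MDS-UPDRS Parts 1–4 ON, and "total Levodopa equivalent daily dose, MoCA, MADRS, NMS-QUEST and PDQ-39".

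The same section gives the purpose. The week 56 assessments "will help to determine whether there is a sustained effect of UDCA on both motor and non-motor aspects of PD". Such a finding is described there as one "which would be in keeping with the assumption of a neuroprotective effect". For the opposite pattern it says that "a rapid deterioration of these clinical parameters after cessation of the study drug would suggest a symptomatic effect of UDCA".

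The treatment-period comparison stands under Secondary outcomes: "The effect of UDCA versus placebo will be assessed as a change from baseline to week 48 for the following secondary outcomes". The outcomes listed there are MDS-UPDRS Part 3 OFF, the ³¹P-MRS metabolites and the sensor measures. The Statistical analysis section plans summaries of change from baseline for the secondary outcomes, and says in general terms that demographic and clinical assessment data will be summarised.

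**The concern.** The question asked of week 56 is whether an effect lasts once the drug is withdrawn. To answer it one must know whether the arms differed at week 48 and whether they still differ at week 56. The outcome as defined is the movement between those two visits. No movement means a lasting effect only if there was an effect to begin with, and the section does not make its reading conditional on a week-48 difference.

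For Part 3 OFF the missing half can be taken from the secondary outcomes. For the other six measures it cannot, because no contrast from the pre-treatment value to week 48 is named. Yet the section asks about non-motor aspects, and the non-motor and quality-of-life scales are all among those six.

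Two uses of the data are at stake. One is the neuroprotective-versus-symptomatic interpretation of the washout visit. The other is the aim, stated under Sample size, that secondary and exploratory data will supply effect sizes and variances for phase III planning. An 8-week off-drug change in PDQ-39 or MoCA is not a treatment effect size.

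**Working it through.** The article gives no power or effect figure for the week 56 outcomes, so there is nothing to reproduce. The check lists which contrasts are named, then works out what the 48–56 contrast is expected to show under different drug effects.

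**Step 1: contrasts named in the article**

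| Measure | Pre-treatment to 48 | Pre-treatment to 56 | 48 to 56 |
|---|---|---|---|
| MDS-UPDRS Part 3 OFF | yes (secondary) | no | yes |
| MDS-UPDRS Parts 1–4 ON | no | no | yes |
| Levodopa equivalent dose | no | no | yes |
| MoCA, MADRS | no | no | yes |
| NMS-QUEST, PDQ-39 | no | no | yes |

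Table 1 schedules a pre-treatment and a week-48 assessment of each scale: baseline for MDS-UPDRS, PDQ-39 and NMS-QUEST, screening for MoCA and MADRS. Levodopa equivalent dose can be derived from the concomitant medication review, which takes place at every visit.

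**Step 2: inputs for Part 3**

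- Natural progression, from Motor measures: Part 3 "scores were observed to increase (deteriorate) by 2.4 points per year".
- Size of a symptomatic effect: 3.25 points, the minimal clinically important improvement given in the same section, used here as a benchmark.
- Size of a neuroprotective effect: 50% slowing. This is an assumption; the article gives no figure.

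Natural change is 2.4 × 48/52 = 2.22 points to week 48, 2.4 × 56/52 = 2.58 to week 56, and 2.4 × 8/52 = 0.37 over the washout.

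**Step 3: expected UDCA minus placebo, in points (negative favours UDCA)**

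| Scenario | 0–48 | 0–56 | 48–56 |
|---|---|---|---|
| Inert drug | 0 | 0 | 0 |
| 50% slowing, benefit kept, slowing stops at week 48 | -0.5 × 2.22 = -1.11 | -1.11 | 0 |
| 50% slowing that continues | -1.11 | -0.5 × 2.58 = -1.29 | -0.18 |
| Symptomatic 3.25 points, not yet washed out | -3.25 | -3.25 | 0 |
| Symptomatic 3.25 points, fully washed out | -3.25 | 0 | +3.25 |

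The last column isolates only the fully washed-out symptomatic effect. The other four rows give 0 or -0.18. Either of the first two columns separates the inert drug from a retained benefit and from an unwashed symptomatic effect. No column by itself distinguishes those last two mechanisms, since both can leave a stable difference at weeks 48 and 56.

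For the other six measures the article gives no progression rate, so no point values can be computed. The logic is the same: an arm difference that does not move between weeks 48 and 56 may be zero at both visits or non-zero at both.

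**Step 4: precision**

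With 20 and 10 patients, the 95% confidence interval half-width for an arm difference is t(0.975, 28) × √(1/20 + 1/10) = 2.048 × 0.3873 = 0.79 SD. The article gives no SD of change. For an assumed 4 to 8 points this is 3.2 to 6.3 points. The factor 0.79 holds for any comparison of these two arms, so it does not favour one contrast over another.

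**The case against.** The strongest reply is that the section is discursive and sets no decision rule. It asks about a sustained effect, which presupposes an effect, and its language is tentative. A reader might infer that the protocol would credit an inert drug with neuroprotection. The text does not support that: it never says that absence of deterioration indicates neuroprotection, and for Part 3 OFF the secondary comparison would be expected to show nothing for an inert drug to sustain.

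A reader might also infer that change over the treatment period is not analysed at all. That is wrong for Part 3 OFF, where it is a secondary outcome. For the other scales, the general statement that clinical assessment data will be summarised may well yield descriptive tables by visit.

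A third tempting inference is that no deterioration will usually be found whatever UDCA does. The numbers do not carry it. A wide interval means imprecision, the SDs are assumed, and at an SD of 4 the power (normal approximation) to detect full loss of a 3.25-point effect is 56%, so it would be detected more often than missed. At an SD of 8 it is 18%.

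The article also limits its own inference. The limitations list says that firm conclusions on neuroprotection will not be possible, and Sample size says that the exploratory outcomes are unpowered and will be read through trends and confidence intervals for estimated differences. Finally, this is a condensed article, and a full protocol or SAP may name more contrasts.

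All of this stands and limits the weight of the point. It does not remove it. The sentence in the article defines the exploratory outcomes rather than giving an example of them, and the contrast it fixes does not answer the question set two sentences later. For six measures, nothing else named in the article fills the gap.

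**Conclusion.** The point holds as a mismatch between a defined contrast and its stated purpose. The week 48–56 change has an expected between-arm difference of about zero (0 to -0.18 Part 3 points) for an inert drug, a retained neuroprotective benefit and a symptomatic effect not yet washed out. Six of the seven measures have no named contrast that could show an effect to be sustained, and none of the seven has a named contrast from the pre-treatment value to week 56.

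The point values rest on the article's 2.4 points per year, an assumed 50% slowing, and 3.25 points as a benchmark symptomatic effect. The zeros for the inert drug, the stable retained benefit and the unwashed symptomatic effect do not depend on those sizes. The finding is confined to what the article defines. It affects exploratory outcomes in an unpowered pilot and leaves the primary outcome untouched.

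**What to change.** For each of the seven measures, estimate the UDCA–placebo difference in change from the pre-treatment value to week 48 and to week 56, adjusted for the pre-treatment value, with 95% confidence intervals. For MoCA and MADRS the pre-treatment value is the screening one, which may precede baseline by up to 8 weeks; say so. For Part 3 OFF the week-48 estimate already exists as a secondary outcome and need only be cross-referenced.

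Report the between-arm 48–56 change as the washout contrast. State that it is read as a sustained or lost effect only alongside the week-48 difference, and that on its own it is not evidence of neuroprotection.

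Reconcile NMS-QUEST at week 56. The text of Assessment procedures and the Exploratory outcomes list both require it, but Table 1 shows it only at baseline and week 48; under the table its 48–56 change could not be computed.

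The cost is some rewording and a few more unpowered exploratory estimates, which should be labelled as such. No visit is added.

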### Sample size

The primary outcome of interest for this study is the safety and tolerability of UDCA which will be assessed by comparing the rate of SAEs in the UDCA and placebo groups, alongside review of adverse treatment reactions and study completion. As the study is a pilot, it is not powered to compare the SAE rate between the groups statistically, but any SAEs in either group will be presented descriptively, the placebo group providing a baseline against which to view any SAEs in the UDCA group. Should this study result in no SAEs then it would be of interest to determine how likely it is that a larger study would find an intolerable rate of SAEs. For this purpose, we will consider the rate of SAEs reported in the exenatide PD trial to be tolerable and acceptable (ie, 20%).^15^ In this study, should no SAEs be found in the group receiving UDCA (n=20) then the likelihood that the true SAE rate is less than 20% is 0.990778.

The sample size has not been prospectively adjusted to account for any lost to follow-up. Instead, as the trial is of a relatively short duration we have instead allowed for any participants withdrawing from the study or lost to follow-up before the completion of 12 weeks of treatment to be replaced with a new participant.

The study has not been powered formally for the secondary or exploratory outcome measures, therefore, interpretation will concentrate on observed trends and confidence intervals for estimated differences. The data collected for the secondary and exploratory outcomes will allow the estimation of the effect size and variance in each outcome to facilitate formal power calculations for future phase III studies. Of note, there is currently no longitudinal clinical trial data using either ^31^P-MRS or our sensor-based approached quantification of motor impairment. The collection of such data is critical to allow high-quality future trial design using these novel outcome measures.

### Patient and public involvement

Patient representatives have been involved in the design of the study protocol and have contributed to the generation of participant facing study documentation. Recruitment to the study will be aided by both local PD groups and publicised by The Cure Parkinson’s Trust, Parkinson’s UK and Michael J Fox Foundation. Results will be disseminated to all participants on completion of the trial.

## Outcome measures

### Safety monitoring

At each visit, participants are asked to report any AEs that have occurred since the previous visit. AEs may also be detected by the study team reviewing the patient or through notification by the participant’s primary care physician. All AEs are assessed by a study doctor for their severity, likely relationship to study drug and required action by a study doctor not involved in the blinded assessment of the patient. All SAEs will be recorded and reported to the sponsor regardless of relation to trial treatment within 24 hours. Any suspected unexpected serious adverse reactions will be reported to the sponsor immediately to allow facilitation of unblinding as necessary. All AEs reported will be reviewed by the trial management group, trial steering group and monitored by an independent data monitoring committee.

Unblinding requests from other clinicians responsible for a patient’s care will be handled by the principal investigator (PI) at each site. The PI at each site may also choose to unblind in response to reported AEs as they are reported.

In the event that side effects such as diarrhoea do not resolve and become persistent or intolerable then the patient can have their dose adjusted to their last tolerated dose for the remainder of the study.

All participants will be asked to return unused medication, this medication will be counted and recorded to assess compliance.

### Motor measures

The MDS-UPDRS is currently the most used and validated clinical tool to quantify the disease state of an individual with PD.^18^ The minimal clinically important difference in the MDS-UPDRS part 3 is reported to be an improvement of 3.25 points for detecting minimal, but clinically pertinent, improvement and a deterioration of 4.63 points for observing minimal, but clinically pertinent, worsening.^24^ Over a period of 5 years, MDS-UPDRS part 3 scores were observed to increase (deteriorate) by 2.4 points per year.^25^ However, despite expected annual deterioration being well characterised, rate of decline may still depend on disease stage and therefore contemporaneous placebo control data remains essential to evaluate potential new therapies.

### Neuropsychological measures

The MoCA is a globally used and validated measure of cognitive impairment and has been used a broad range of neurological diseases and study designs.^16^ The MADRS has been validated in PD as a screening tool for major depression.^17 26^

### Non-motor and quality of life measures

NMS-QUEST is a clinical screening tool that covers a wide range of non-motor symptoms.^20^ PDQ-39 is a validated and widely used quality of life questionnaire that covers a range of measures such as emotional well-being, activities of daily living and mobility in the context of PD.^19^ The total equivalent levodopa dose is calculated using calculations and equivalencies generated previously in a systematic review and allows quantitative comparisons between patients on different medication regimes.^27^

### ^31^Phosphorous MR spectroscopy

^31^P-MRS is experienced by the patient in the same manner as a standard clinical MRI scan. As the metabolites of interest are phosphorus based, it provides the opportunity to investigate key metabolites in bioenergetics such as ATP, PCr and Pi which all have clear spectroscopic resonances (figure 1). It is, therefore, an ideal approach to assess mitochondrial function in vivo. Ratio measures such as Pi/ATP and PCr/ATP have been shown to reflect the status of different aspects of oxidative phosphorylation pathways.^28^

**Figure 1 F1:**
[figure not shown]
Representative ^31^P-MRS spectra obtained from the midbrain of a healthy volunteer following appropriate phasing and 10 Hz Lorentzian apodisation with no further editing. From left to right, phosphomonoesters (PME), inorganic phosphate (PI), phosphodiesters (PDE), phosphocreatine (PCr) and the three spectral resonances of adenosine triphosphate (γ-,α-,β-ATP). ^31^P-MRS, ^31^phosphorus MR spectroscopy.

Two-dimensional chemical shift imaging (CSI) with image-selected in vivo spectroscopy will be used for spectral spatial localisation,^29 30^ with a dedicated multinuclear MRI system (Ingenia 3.0T, Philips Healthcare, Best, NL) and dual-tuned ^1^H/^31^P head coil (Rapid Biomedical, Würzburg, Germany). Standard clinical T1 and T2-weighted imaging will allow the alignment of the two ^31^P axial CSI sequences as shown in figure 2. The two sequences will be aligned to obtain spectra from both the putamen (voxels for both anterior and posterior putamen bilaterally) and the midbrain (one voxel for each left and right). This is a clear advantage over alternative techniques that typically use surface coils as it allows the localisation of spectra to these specific brain regions typically involved in early PD. Imaging both anatomical regions is of importance as one mechanism of mitochondrial dysfunction in PD may be that of retrograde axonal degeneration, therefore, spectra from the striatum may show clear mitochondrial dysfunction even in early disease independent of findings in the midbrain. Previous cross-sectional work using a similar ^31^P-MRS protocol has demonstrated reductions in ATP and PCr in PD compared with controls in both the putamen and midbrain.^31^ Additionally, a further study demonstrated that Pi/ATP ratios were increased in PD compared with controls.^32^

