**Trial registration number:**

NCT03840005.

Strengths and limitations of this studyThis is the first double-blind, randomised, placebo-controlled trial of ursodeoxycholic acid (UDCA) in Parkinson’s disease (PD).This study uses novel secondary outcomes not previously used in a clinical trial studying PD; namely ^31^Phosphorus MR spectroscopy (^31^P-MRS) of disease-specific regions and detailed, complementary home and clinic-based motor activity and gait analysis.^31^P-MRS will allow the assessment of mitochondrial dysfunction directly in the midbrain, including the substantia nigra, the most severely affected brain area in PD.A limitation of the study is the considerable number of capsules patients will have to take; patients will on average be taking an additional nine extra capsules of medication each day through the trial, significantly increasing their ‘pill burden’.A further limitation is the small sample size of n=30 with 20 patients on UDCA and 10 patients on placebo, it will not be possible to draw firm conclusions about the neuroprotective effect of UDCA in PD but will allow for appropriate power and sample size calculations for future studies.

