**Figure 2 F2:**
[figure not shown]
The substantia nigra slice is placed to cover the midbrain with the highlighted voxels of interest for subsequent analyses highlighted in yellow in the sagittal (A) and axial planes (B). Placement of ^31^P-MRS slices. The basal ganglia slice is placed over the putamen aligned in both the coronal (C) axial planes (D), and voxels of interest for subsequent analyses are highlighted in yellow. One voxel covers the anterior putamen and another the posterior putamen.

Details of the acquisition sequences are shown in table 2. Spectra will be processed in the time domain using jMRUI software V.5.2 (http://www.jmrui.eu) and the Advanced Method for Accurate, Robust and Efficient Spectral fitting (AMARES) algorithm is used to determine the relative area under each peak.^33–35^ Analysis of the ^31^P-MRS data will focus on the change between randomisation and week 48 of normalised amplitudes of ATP, PCr and Pi, and ratio values such as PCr/ATP and Pi/ATP that assess bioenergetic dysfunction. All STH patients will undergo ^31^P-MRS. UCLH patients are also invited to attend the STH site for ^31^P-MRS.

**Table 2 T2:** Detailed parameters of the ^31^P protocol for acquisition

Sequence description	Localisation	Decoupling, NOE	TR (ms)	TE (ms)	NSA	Acquired voxel size (mm)	Reconstruction matrix	Reconstructed voxel size (mm)	Scan duration (min)
^31^P-Basal Ganglia	^31^P 2D CSI ISIS localisation	On	4000	0.22	10	40×40×20	12×12	17.5×17.5×20	12:48
^31^P-Substantia Nigra	^31^P 2D CSI ISIS localisation	On	4000	0.22	8	40×40×20	14×14	15×15×20	10:16

CSI, chemical shift imaging; ISIS, image-selected in vivo spectroscopy; NOE, nuclear overhauser efect; NSA, number of signal averages; TE, time to echo; TR, time to repetition.

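### Spectra are presented as specific to left and right midbrain and to anterior and posterior putamen, but Table 2 shows a 40×40×20 mm acquisition that cannot separate them

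*Protocol article*

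**What the plan says.** 31P-MRS is the secondary outcome that is meant to confirm target engagement (Abstract; Secondary outcomes). The section on 31Phosphorous MR spectroscopy lists the regions sampled: "voxels for both anterior and posterior putamen bilaterally) and the midbrain (one voxel for each left and right". That makes four putamen voxels and two midbrain voxels. The section presents this as a clear advantage over surface-coil techniques, because "it allows the localisation of spectra to these specific brain regions typically involved in early PD". The Figure 2 legend adds: "One voxel covers the anterior putamen and another the posterior putamen". Among the study's strengths, the article states that the method "will allow the assessment of mitochondrial dysfunction directly in the midbrain, including the substantia nigra".

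Table 2 gives the acquisition. Both sequences have an acquired voxel of 40×40×20 mm. The basal-ganglia sequence is reconstructed on a 12×12 matrix at 17.5×17.5×20 mm, and the substantia nigra sequence on a 14×14 matrix at 15×15×20 mm. The text does not comment on the gap between the two resolutions and does not mention partial volume.

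**The concern.** Spatial resolution is set by what is acquired. Reconstructing on a finer matrix gives a smoother map, but it cannot separate tissue that the acquisition did not separate. The regional labels in the text match the reconstructed voxels, while the signal in each spectrum comes from a much larger volume.

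The interpretation of the target-engagement outcome is at stake. With these labels, a reader may take a change in a midbrain voxel as a change in the substantia nigra, or take left and right midbrain, or anterior and posterior putamen, as separate pieces of evidence. Two voxels that mostly share signal will tend to agree whatever the biology, and that agreement is not replication. Nor would an absence of change at this resolution exclude a change confined to a small structure inside the voxel.

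**Working it through.** All inputs are from Table 2: TR 4000 ms for both sequences; NSA 10 (basal ganglia) and 8 (substantia nigra); scan durations 12:48 and 10:16; and the voxel sizes and matrices given above.

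**1. Is the 40 mm entry a misprint?**

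Field of view = matrix × reconstructed voxel (inferred; the article does not state it):
- Basal ganglia: 12 × 17.5 = 210 mm
- Substantia nigra: 14 × 15 = 210 mm

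Field of view / acquired width = 210 / 40 = 5.25, or about a 5×5 acquired grid.

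Encodings per signal average = duration / TR / NSA:
- Basal ganglia: 768 s / 4 s / 10 = 19.2
- Substantia nigra: 616 s / 4 s / 8 = 19.25

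Both are exactly 19 if two start-up repetitions are assumed: (192 − 2)/10 and (154 − 2)/8.

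Times under other grids (encodings × NSA × TR):

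| Grid | Basal ganglia | Substantia nigra |
|---|---|---|
| Full reconstruction matrix (144; 196) | 96.0 min | 104.5 min |
| Full 5×5 (25) | 16:40 | 13:20 |
| 5×5 without corners (21) | 14:00 | 11:12 |
| Stated | 12:48 | 10:16 |

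The stated times rule out encoding the full 12×12 or 14×14 matrix at this TR and NSA. They imply a coarse grid of about 19 encodings. That is somewhat fewer than a full or corner-cut 5×5 grid, so the exact scheme is not known. The 40 mm entry is of the right order and does not look like an error.

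**2. Volumes**

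- Acquired: 40 × 40 × 20 mm = 32.0 mL
- Reconstructed, basal ganglia: 17.5 × 17.5 × 20 mm = 6.125 mL; 32.0 / 6.125 = 5.2
- Reconstructed, substantia nigra: 15 × 15 × 20 mm = 4.5 mL; 32.0 / 4.5 = 7.1

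**3. Overlap of neighbouring voxels**

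This assumes that the paired voxels are adjacent on the reconstructed grid. Overlap of nominal acquired widths along the shared axis = 1 − spacing / 40:
- Midbrain: 1 − 15/40 = 62.5%
- Putamen: 1 − 17.5/40 = 56.25%

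**4. Point-spread response at the neighbour's centre**

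For Fourier encoding, the response at distance d is the mean of cos(2πkd/210) over the encoded steps k along that axis. For a 5×5 grid, k runs from −2 to 2:
- Midbrain (d = 15): (1 + 2 × 0.901 + 2 × 0.623)/5 = 0.81
- Putamen (d = 17.5): (1 + 2 × 0.866 + 2 × 0.5)/5 = 0.75

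For the 21-point grid, the steps k = 0, ±1 and ±2 carry 5, 10 and 6 encodings:
- Midbrain: (5 + 10 × 0.901 + 6 × 0.623)/21 = 0.85
- Putamen: (5 + 10 × 0.866 + 6 × 0.5)/21 = 0.79

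For an ideal 40 mm sinc response, sin(πd/40)/(πd/40):
- Midbrain: 0.78
- Putamen: 0.71

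Across these schemes the response is about 0.7 to 0.85 of peak. It describes how much signal the neighbours share; it is not an estimate of the correlation between patients' measured values.

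**The case against.** The strongest reply is that nothing is hidden and nothing improper is planned. Table 2 has separate columns for acquired and reconstructed size. The outcome is defined as metabolite levels from multi-voxel brain spectroscopy, and no analysis by side, by putamen subregion or of the nigra alone is specified. The strengths statement includes the nigra within the midbrain and does not claim to isolate it. The Sample size section says that the secondary outcomes are unpowered and will be read through trends and confidence intervals. How voxels are combined may be settled in the full protocol or the analysis plan.

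Much of this stands, and it limits the point. Four stronger readings are tempting but unsupported:

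- *The advantage over surface-coil work fails.* The Discussion says the earlier study of UDCA in PD acquired only occipital spectra. Slices at midbrain and at basal-ganglia level may well be an advantage over that, even at 40 mm in-plane.
- *A nigral effect would appear at one seventh of its size.* The ratio 32/4.5 gives about 7, but this treats the reconstructed voxel as the target tissue and ignores point-spread weighting. The article gives no anatomical volumes, so the dilution cannot be computed.
- *The trial will conclude that UDCA restored ATP in the nigra, or failed to.* No section plans that inference; the labels only invite it.
- *All regional information is lost.* The 20 mm slice thickness is the same acquired and reconstructed, so the two levels stay distinct. Left and right putamen are presumably further apart and less affected. The article also cites cross-sectional work with a similar method that found differences in both putamen and midbrain; that supports region-level sensitivity, not sub-regional separation.

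Disclosure in a table does not correct prose that attributes a finer property to the same data, and no later analysis plan can restore resolution that was not acquired.

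**Conclusion.** The localisation is overstated as written. The text and the Figure 2 legend present left and right midbrain, and anterior and posterior putamen, as separately sampled, yet the acquired voxel is 5.2 to 7.1 times the volume of the reconstructed voxels. If the paired voxels are adjacent, they share about 56% to 62% of their nominal width and are largely the same signal.

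The acquired size is stated in Table 2 and is consistent with its scan times. The overlap and point-spread figures rest on assumed adjacency, an inferred 210 mm field of view and idealised encoding schemes, none of which exactly reproduces the stated durations. The range 0.7 to 0.85 is therefore indicative. The consequence is confined to a secondary outcome: it limits what target engagement can be said to show about the nigra, about midbrain side and about putamen subregion. It does not invalidate the spectroscopy.

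**What to change.** - In the strengths list, the section on 31Phosphorous MR spectroscopy and the Figure 2 legend, describe the spectra as centred on the midbrain and on the putamen, acquired at 40×40×20 mm, with partial volume from surrounding tissue.
- Do not treat left and right midbrain voxels, or anterior and posterior putamen voxels, as independent or separately interpretable. One way is to analyse one averaged midbrain value and one averaged putamen value per side, giving three values per participant instead of six. Averaging does not recover resolution; it only stops shared signal from being counted as separate evidence.
- State that neither a positive nor a null result can be attributed specifically to the substantia nigra.

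The cost is wording and the averaging of spectra already acquired; no rescanning is needed. The downside is a less favourable imaging claim and fewer sub-regional read-outs.
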